# An open-label prospective pilot trial of nucleus accumbens deep brain stimulation for children with autism spectrum disorder and severe, refractory self-injurious behavior: study protocol

**DOI:** 10.1186/s40814-022-00988-3

**Published:** 2022-02-02

**Keywords:** Autism spectrum disorder, Deep brain stimulation, Children, Self-injurious behavior, Nucleus accumbens

## Abstract

**Background:**

Children and youth with autism spectrum disorder (ASD) may manifest self-injurious behaviors (SIB) that may become severe and refractory with limited pharmacologic or behavioral treatment options. Here, we present the protocol of a prospective, mixed-methods study to assess the safety and efficacy of deep brain stimulation (DBS) of the nucleus accumbens (NAcc) for children and youth with ASD and severe, refractory SIB.

**Methods:**

This is a prospective, single-center, single-cohort, open-label, non-randomized pilot trial of 6 patients. Participants will be recruited through specialized behavioral clinics with persistent severe and refractory SIB following standard and intensive interventions. Following NAcc-DBS, participants will be enrolled in the study for 12 months. The primary objectives of the study are safety and feasibility, assessed by rate of recruitment and identification of factors impacting adherence to follow-up and study protocol. Potential treatment efficacy will be assessed by changes in the Children’s Yale-Brown Obsessive-Compulsive Scale in ASD (CYBOCS-ASD), the Behavior Problems Index (BPI), the Inventory of Statements about Self-Injury (ISAS) and the Repetitive Behavior Scale-Revised (RBS-R) questionnaires. Additional clinical outcomes will be assessed, including measures of participant and caregiver quality of life, actigraph measurements, and positron emission tomography (PET) changes following DBS.

**Discussion:**

This study will be the first to evaluate the effect of DBS of the NAcc on a pediatric population in a controlled, prospective trial. Secondary outcomes will improve the understanding of behavioral, neuro-imaging, and electrophysiologic changes in children with ASD and SIB treated with DBS. This trial will provide an estimated effect size of NAcc-DBS for severe refractory SIB in children with ASD in preparation for future comparative trials.

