### Enrollment and surgery

Potential participants are recruited from specialized behavioral clinics. Potential participants are reviewed by the investigators with respect to inclusion and exclusion criteria (Table 2). Eligible patients are discussed in a multidisciplinary meeting of the surgical, psychiatric and medical teams. There are no changes to the participants’ medications or behavior therapies after enrollment prior to surgery. Any changes to medications following surgery are noted, including changes to dosages and indication for change.

**Table 2 Tab2:** Study inclusion and exclusion criteria

*Inclusion criteria*	
1. Children and adolescents between age 7-18	
2. Diagnosed with autism spectrum disorder by a treating developmental pediatrician	
3. Failure or non-eligibility of medical therapy with ongoing repetitive self-injurious behaviors, at 6 months or more after instigation of therapy. Failure is defined as a lack of improvement in self-injurious behaviors, as documented by objective evidence, including caregiver logs or clinician assessment, if the clinician has documented a baseline status prior to instigation of the medical therapy.	
4. The child has undergone rigorous, gold-standard Functional Behavior Assessment including functional analysis, leading to treatment lasting a minimum of 6 months, without significant change from baseline.	
5. Diagnosis of secondary stereotypies, based on clinical assessment of the treating physicians with evidence of self-injury, documented in the patient records. The definition of self-injury is contextual, but requires current, previous or potential manifestation of physical injury to the child.	
6. The child is at risk of permanent injury as a result of self-injurious behaviors. Permanent injury is non-reversible physical injury causing a reduction in baseline functions.	
7. Parents or legal guardians, including caregivers, informed, and able to give written consent.	
8. Able to comply with all testing, follow-ups and study appointments and protocols for 12 months following the end of the duration of the study.	
*Exclusion criteria*	
1. Does not meet study specific definition of autism spectrum disorder using DSM-5 criteria. The treating physicians at each individual clinic will be responsible for diagnosis.	
2. Substance dependence or abuse in the last 6 months, excluding caffeine and nicotine	
3. Any contraindication to MRI, required for stereotactic surgical planning.	

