### Sample size and recruitment

In this prospective, controlled trial, six patients are selected to determine safety and initial potential efficacy, as it typical for most DBS early phase trials. There is no control group, and each patient will serve as a comparator for primary outcome measures.

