## Discussion

The current paper presents a single-cohort, open-label, non-randomized, prospective pilot trial for the first controlled study of DBS of the NAcc for severe, refractory SIB in children and youth with ASD. This study is important to understand feasibility, safety, and treatment response. It is critical to establish feasibility of DBS for this novel indication and vulnerable patient population.

The rapid expansion of DBS indications in adult pathologies has allowed for treatment of many psychiatric diseases [58–60]. It is expected that the adaptation of DBS for children will be feasible for SIB. The early treatment of SIB in childhood could potentially be beneficial during critical windows of development such as in the adolescent or young adult years. The largest feasibility challenge of this study will be recruitment of vulnerable participants. This is mitigated by a multi-disciplinary team who are familiar with the patient population and the trial to allow for multiple sources of referral. Furthermore, results of a pilot trial should greatly improve recruitment in a future definitive trial. The use of multiple clinical measurement tools may help determine the optional composite measure of responsiveness of SIB to DBS. Although the quantitative data may not be rigorous enough to calculate a minimally clinical important difference, an estimated effect size may help determine sample size. Careful measurement and analysis of feasibility in this unique trial will be critical in the design of future research.

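### The article calls a single-arm pre-post pilot controlled and promises an effect size of NAcc-DBS, but six patients without a comparator can yield only an imprecise within-patient change

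*Protocol article*

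**What the plan says.** All references are to the Protocol article.

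**The label.** Three places call the study controlled:
- Abstract, Discussion paragraph: "This study will be the first to evaluate the effect of DBS of the NAcc on a pediatric population in a controlled, prospective trial".
- Sample size and recruitment: "In this prospective, controlled trial, six patients are selected to determine safety and initial potential efficacy".
- Main Discussion: "prospective pilot trial for the first controlled study of DBS of the NAcc for severe, refractory SIB".

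**The design.** The abstract's Methods paragraph says "This is a prospective, single-center, single-cohort, open-label, non-randomized pilot trial of 6 patients". The sentence after the label in Sample size and recruitment begins "There is no control group" and makes each patient their own comparator. Data management and statistical analysis says that nobody is blinded and that there are no blinded periods with stimulation on or off. According to Follow-up, the outcome scales are given once before surgery and four times after it. Clinical outcome measures defines efficacy as the percent change within each subject from baseline to week 52.

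**The promise.** The abstract says, without qualification, "This trial will provide an estimated effect size of NAcc-DBS for severe refractory SIB in children with ASD", with later comparative trials in view. The main Discussion is softer: "an estimated effect size may help determine sample size". That same sentence doubts that the data can support a minimally important difference, and Strengths and limitations says that the small cohort limits the clinical analyses.

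**The concern.** A control is what allows a change to be attributed to treatment. This design has no concurrent comparator, no sham or off phase, and a single reading on the outcome scales before surgery. Several things other than stimulation can move the week-52 score:
- the operation and the close follow-up around it;
- caregivers who report the outcome and know that the child has been implanted;
- some regression to the mean, because children enter with severe behaviour and have one baseline reading;
- treatment changes after surgery, which the plan allows for: "Any changes to medications following surgery are noted, including changes to dosages and indication for change".

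Two things are at stake. One is the conclusion: a reader of the abstract would take the result to be the effect of DBS shown in a controlled trial. The other is the next trial: a comparative trial needs the difference between groups, and a pre-post change is a different quantity even when it is estimated without error.

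**Working it through.** **Stated figure.** The sample size is 6, justified by custom in early DBS trials. The article gives no alpha, power, effect size, SD or precision target, so there is no calculation to reproduce. The check is what six patients can deliver.

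**Inputs.** n = 6 and 5 degrees of freedom, from the article. The values of d below (mean change divided by the SD of the change) are assumptions, because the article gives none.

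**1. Precision of the mean change.** The 95% half-width is t(0.975; 5)/√6 = 2.571/2.449 = 1.05 SD of the change.

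**2. Precision of the standardised change.** The observed t is d√6. The noncentral-t distribution gives the two noncentrality values that put 2.5% in each tail, and dividing these by √6 gives the limits for d. The last two columns apply 2(1.960 + 0.842)²/d² = 15.70/d² per arm (two arms, two-sided 5%, 80% power, normal approximation), as if d were a between-group effect. They are computed from unrounded limits and rounded up.

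| Observed d | 95% CI for d | Per arm at d | Per arm across the CI |
|---|---|---|---|
| 0.5 | -0.38 to 1.33 | 63 | 9 to no finite number |
| 0.8 | -0.16 to 1.71 | 25 | 6 to no finite number |
| 1.0 | -0.03 to 1.97 | 16 | 5 to no finite number |
| 1.5 | 0.27 to 2.68 | 7 | 3 to 223 |

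**3. Precision of the SD.** The multipliers are √(5/12.83) = 0.62 and √(5/0.831) = 2.45. A sample size goes with the square of the SD, so across this interval it varies by 12.83/0.831 = 15.4, about 15-fold.

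**4. The quantity itself.** Write the observed change as S + N, where S is the effect of stimulation and N is everything else listed under the concern. A one-arm pre-post design estimates S + N. A randomised comparison estimates S, because N is expected in both arms. Nothing in the definition of efficacy separates the two, and more patients would narrow the interval without removing N. The article does not give the size of N.

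**The case against.** **Each patient is their own comparator, and the design is disclosed.** Both are true. The article repeatedly says single-cohort, open-label and non-randomised. But comparing one reading before surgery with week 52 is not a control for time, expectation or co-treatment, and disclosing the design elsewhere leaves the label contradictory.

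**The article already concedes weakness, and nothing depends on efficacy.** The main Discussion only says that an effect size may help with sample size, and the stated threshold for progression is recruitment. This stands and limits the consequence. However, what is conceded is imprecision. The missing comparator is not mentioned, and the abstract carries no hedge.

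**The design has more than one pre-stimulation reading.** This is partly right. A self-injury log and optional two-week actigraphy are also planned before surgery. Patients go home with the stimulator off, programming starts at weeks 4 to 6, and the scales are repeated at week 4. That reading could partly separate surgery from stimulation, but the definition of efficacy does not use it in that way.

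**Stronger readings that the documents do not support:**
- *The next trial will be undersized.* This would require the pilot's point estimate to be used directly, which the article does not say, and a non-stimulation component of known size. Imprecision alone can err in either direction.
- *Regression to the mean is large.* Entry requires at least 6 months of failed treatment after functional assessment, and sets no threshold on the outcome scales. Some regression is possible, but the article gives no basis for a figure.
- *Behaviour-therapy changes after surgery go unrecorded.* The article mentions only medication changes, but it is a condensed account and its silence shows nothing about the full protocol.

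**Conclusion.** The article is wrong as written on two points. It gives the trial a property, being controlled, that its own description denies, and it promises an effect of NAcc-DBS where the design can estimate only a within-patient change.

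The precision figures follow from n = 6, assuming approximately normal changes: ±1.05 SD for the mean change, -0.03 to 1.97 for an observed d of 1.0, and 0.62 to 2.45 times the estimate for the SD. The values of d are illustrative. The bias is described only in kind, because the documents do not allow it to be quantified.

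The pilot remains useful for recruitment, completion, safety and, roughly, variability. The primary objectives of feasibility and safety do not depend on this point. It should be corrected because it changes what the trial may conclude.

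**What to change.** 1. Delete the word controlled in the abstract's Discussion paragraph, in Sample size and recruitment, and in the first paragraph of the main Discussion.
2. Reword the abstract, and align the main Discussion with it: the trial will estimate the within-patient pre-post change and its SD, each with a 95% confidence interval, and this change cannot be attributed to stimulation alone.
3. State that a definitive trial will be sized on a minimum worthwhile between-group difference and not on the pilot's point estimate. The pilot SD may inform it cautiously, for example through an upper confidence limit. The 97.5% limit (2.45 times the estimate) multiplies a sample size by 2.45² = 6.0. The one-sided 80% limit (1.46 times) multiplies it by 1.46² = 2.1. A confidence limit of d should not be used for sizing, because for d = 0.8 or 1.0 the lower limit is below zero and gives no finite number.
4. Optionally, present the existing week-4 scales, where completed before programming starts, as a post-implant reading with stimulation off. A second baseline questionnaire before surgery is also optional. It would show drift before the operation, but anticipation of surgery could affect it.

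Items 1 to 3 cost only wording. The week-4 presentation uses data already scheduled. A second baseline would add one more round of questionnaires for families. None of this changes clinical management.

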**Trial registration:**

Registration on ClinicalTrials.gov was completed on 12 June 2019 with the Identifier: NCT03982888.

## Background

Autism spectrum disorder (ASD) is a clinical diagnosis based on a set of heterogeneous neurodevelopmental conditions. ASD is characterized by difficulties in social interaction, communication, repetitive restricted behaviors according to the Diagnostic and Statistical Manual of Mental Disorders, 5th edition (DSM-V) [1]. ASD has a worldwide prevalence of 1%, an estimated 1 in 68 births in the USA in 2014 by the Center for Disease Control and Prevention, and a greater prevalence in males than females [2–4].

The behavioral comorbidities of ASD include aggressive behavior (up to 68%) [5, 6] and repetitive self-injurious behavior (up to 50%) [7, 8]. In children with ASD and self-injurious behaviors (SIB), over 75% of children will have persistence of these behaviors into adulthood, sometimes resulting in severe harm and even death [5, 9–11]. SIB can be defined as repetitive “behavior which produces physical injury to the individual’s own body” with several different subclassifications [12]. Pharmacologic agents, such as antipsychotics (e.g., risperidone, aripiprazole), and selective serotonin reuptake inhibitors (e.g., fluoxetine) show evidence for treating irritability but not specifically reducing self-injury [13–17].

Applied behavior analysis, based on operant methodology, offers an evidence-based method to assess and treat SIB. Functional analysis identifies the function of the behavior and shows what conditions self-injury are associated with and what stimulus conditions maintain it [18]. It is hypothesized that social consequences, such as escape from demands or selective attention, mediate 20–25% of SIB through automatic reinforcement [12, 19]. Subtypes of automatic reinforcement show differential responses to reinforcement-based interventions and may have implications on the biological bases of SIB and biobehavioral research. This may also give us insight into the role of neuromodulation as a feasible intervention for SIB.

### Study design

We present a protocol for a single-center, single-cohort, open-label, non-randomized prospective pilot trial of NAcc-DBS for refractory and severe SIB in children with ASD. The trial is currently open for recruitment at the Hospital for Sick Children (HSC) in Toronto.

### Goals and objectives

The primary objective of the study is to assess feasibility and safety, measured by recruitment rate, identification of factors impacting follow-up and protocol adherence, and successful implantation. Secondary clinical objectives include change in frequency or severity of SIB following surgery, measured regularly by caregiver-reported questionnaires over the course of 1 year. Additional clinical outcomes include changes quality of life for the patient and their caregiver(s), repetitive motion characteristics as measured with actigraphy, metabolic changes seen through positron emission tomography (PET), and changes on electrophysiologic data. To our knowledge, this is the first prospective trial of DBS for children with SIB and represents the first assessment of a potential surgical treatment for patients with extremely limited therapeutic options.

## Methods/design

This is a prospective, single-center, open-label, non-randomized study of six patients at HSC. The aim is to evaluate the feasibility and safety of DBS of the NAcc for medically refractory, repetitive self-injurious behaviors in children with ASD. Electrophysiological parameters are optimized in the 12-month follow-up to study and manage possible side effects.

### Ethics and registry

This research involves human participants and is performed in accordance with the Delcaration of Helsinki. This trial was approved by the Hospital for Sick Children Research Ethics Board, approval number 1000060282. Registration on ClinicalTrials.gov was completed in June of 2019 with the Identifier: NCT03982888. Patient recruitment and continuation in the study is considered by a safety monitoring board at HSC. Written informed consent to participate in the trial is acquired from the child or adolescent when able, or the parent or legal guardians. If the child or adolescent is unable to provide consent, assent is sought.

### Enrollment and surgery

Potential participants are recruited from specialized behavioral clinics. Potential participants are reviewed by the investigators with respect to inclusion and exclusion criteria (Table 2). Eligible patients are discussed in a multidisciplinary meeting of the surgical, psychiatric and medical teams. There are no changes to the participants’ medications or behavior therapies after enrollment prior to surgery. Any changes to medications following surgery are noted, including changes to dosages and indication for change.

**Table 2 Tab2:** Study inclusion and exclusion criteria

*Inclusion criteria*	
1. Children and adolescents between age 7-18	
2. Diagnosed with autism spectrum disorder by a treating developmental pediatrician	
3. Failure or non-eligibility of medical therapy with ongoing repetitive self-injurious behaviors, at 6 months or more after instigation of therapy. Failure is defined as a lack of improvement in self-injurious behaviors, as documented by objective evidence, including caregiver logs or clinician assessment, if the clinician has documented a baseline status prior to instigation of the medical therapy.	
4. The child has undergone rigorous, gold-standard Functional Behavior Assessment including functional analysis, leading to treatment lasting a minimum of 6 months, without significant change from baseline.	
5. Diagnosis of secondary stereotypies, based on clinical assessment of the treating physicians with evidence of self-injury, documented in the patient records. The definition of self-injury is contextual, but requires current, previous or potential manifestation of physical injury to the child.	
6. The child is at risk of permanent injury as a result of self-injurious behaviors. Permanent injury is non-reversible physical injury causing a reduction in baseline functions.	
7. Parents or legal guardians, including caregivers, informed, and able to give written consent.	
8. Able to comply with all testing, follow-ups and study appointments and protocols for 12 months following the end of the duration of the study.	
*Exclusion criteria*	
1. Does not meet study specific definition of autism spectrum disorder using DSM-5 criteria. The treating physicians at each individual clinic will be responsible for diagnosis.	
2. Substance dependence or abuse in the last 6 months, excluding caffeine and nicotine	
3. Any contraindication to MRI, required for stereotactic surgical planning.	
4. Likely to relocate away from the study site or move during the study’s 1-year duration	
5. Presence of cardiac arrhythmias, coagulopathy or other cardiac, respiratory, renal, or endocrine conditions that will result in significant risk from a surgical procedure.	
6. Pregnancy	

Participants are assessed by the anesthesia service, neuropsychology team, and receive a magnetic resonance image (MRI) and optional fluorodeoxyglucose (FDG) PET scan. On the day of surgery, a Leksell stereotactic frame is applied under general anesthesia. The patient receives a head computed tomography (CT) scan that is merged to the pre-operative MRI and planned targets. Stereotactic coordinates are calculated and verified to target the NAcc with the goal to include the ALIC in the trajectory of the DBS electrode (Fig. 1 B, C). In the operating room, a curvilinear incision anterior to the coronal suture is made to place the DBS electrodes stereotactically. Thresholds for side effects are recorded intraoperatively. Electrodes are placed with fluoroscopic confirmation and a pulse generator is connected and implanted in the infraclavicular region under the same anesthetic.

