### Clinical outcome measures

This trial will conduct pre-post analyses to compare frequency and severity of SIB in children and youth with ASD before and after DBS intervention. Clinical outcomes are measured by the change between baseline and 1 year in the following validated scales: Children’s Yale-Brown Obsessive-Compulsive Scale in Autism Spectrum Disorder (CYBOCS-ASD) [47, 48], the Behavior Problems Inventory (BPI) [49], the Inventory of Statements about Self-Injury (ISAS) [50] and the Repetitive Behavior Scale-Revised (RBS-R) [51]. These scales were chosen by expert consensus between developmental pediatricians, neurologists, and the neurosurgical team. Although no scale has specifically been validated for children with ASD and SIB, the combination of these scales studied in children with ASD or all-age patients with repetitive behavior will provide an assessment of responsiveness of DBS over time. Secondary clinical outcomes are measured using the Quality of Life Scale 9Peds QL version 4, Aberrant Behavior Checklist [52, 53], and caregiver logs of repetitive self-injurious behaviors. Time to complete each questionnaire and correlation with quality of life will be useful information in the design of a composite primary objective in larger, future trials.

Patients and caregivers complete scales prior to the intervention and also at week 4, 12, week 26, and week 52. Baseline assessments are completed prior to surgery. Efficacy is determined by the within-subject percent change in the primary outcome scores at 1 year (week 52) following surgery compared to baseline.

Additional outcomes include changes in motor patterns based on actigraphy. Actigraphy is the continuous measurement of an individuals’ movement using a device worn similarly to a watch (Axivity AX3 and Axivity AX6) [54, 55]. The Axivity device can quantify movements and has been validated to detect specific behaviors, such as hand flapping, of patients with ASD with 94.6% accuracy [56]. Children have an actigraph placed on their non-dominant wrist 4 weeks prior to the surgery for a total of 2 weeks of recordings. During specific follow-up visits (weeks 12, 26, and 52), the children have the option to wear the actigraph for 2-week intervals. Markers of stereotypies include maximum and minimum value amplitudes, variance, peak to peak, and entropy fast Fourier transform, to be analyzed using MATLAB (Mathworks, Natick, MA) [54, 56].

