### Follow-up

Evaluation and assessments occur at approximately 22 time points from pre- to 1-year post-surgery (Table 3). Participants are followed weekly after surgery by the medical team between weeks 0–6, and monthly after 8 weeks. There are two required MRI scans that fall under the standard of care, two optional FDG-PET scans, and 3 possible 2-week periods of actigraph recordings. Surveys for the primary clinical outcomes and secondary outcomes are administered once prior to the surgery and four times following surgery. DBS programming starts at approximately 4–6 weeks and reassessment and stimulation changes are planned for weeks 12, 26, and 52 unless there are adverse effects, for which there will be additional programming visits. Ongoing follow-up for safety and DBS programming will occur at HSC until participants turn 18 years old, at which point they will be transitioned to adult care.

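### Inclusion criterion 8 asks for compliance for 12 months after a study that itself ends at 12 months, and the age range is not reconciled with a site follow-up limit at age 18

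*Protocol article*

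**What the plan says.** All references are to the protocol article.

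**Length of commitment**
- Table 2, inclusion criterion 8: "Able to comply with all testing, follow-ups and study appointments and protocols for 12 months following the end of the duration of the study".
- Table 2, exclusion criterion 4: "Likely to relocate away from the study site or move during the study’s 1-year duration".
- Abstract, Methods: "Following NAcc-DBS, participants will be enrolled in the study for 12 months".
- Clinical outcome measures: "Efficacy is determined by the within-subject percent change in the primary outcome scores at 1 year (week 52) following surgery compared to baseline".
- Table 3 heads the period beyond week 52 as post-trial. It lists programming every six months or as indicated, annual neurosurgery follow-up and neuropsychology as needed. No questionnaires, actigraphy, PET or self-injury log appear there.

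**Age**
- Table 2, inclusion criterion 1: "Children and adolescents between age 7-18".
- Follow-up: "Ongoing follow-up for safety and DBS programming will occur at HSC until participants turn 18 years old"; care then passes to adult services.
- Study design describes a single-center trial, so no second site takes over study visits.

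**Where eligibility enters an outcome**
- Feasibility and safety defines the recruitment rate as those enrolled over those eligible. The trial is feasible if this rate exceeds 50%, or if six patients are recruited in under 36 months.

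**The concern.** Criterion 8 and exclusion criterion 4 stand in the same table and set different periods of commitment: one runs a year past the end of the study, the other covers the study's single year. A screener who applies criterion 8 as written could turn away a family able to attend everything through week 52 but unable to commit beyond it. A screener who applies the apparent intent would count that family as eligible. Since the eligible count is the denominator of a primary feasibility measure, the two screeners could report different rates from the same referrals.

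The age question concerns follow-up to the endpoint. A participant can meet inclusion criterion 1 and still turn 18 before week 52. The Follow-up section places safety and programming follow-up at the site only until that birthday. Safety is a primary objective, efficacy is read at week 52 and there are six patients, so the plan should not leave open what happens to such a participant.

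**Working it through.** **1. Check of the schedule.** The Follow-up section gives approximately 22 time points from before surgery to one year. Counting distinct visits in Table 3:

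- enrollment: 1
- surgery: 1
- weekly, weeks 1 to 6: 6
- every four weeks, weeks 8 to 56: (56 − 8)/4 + 1 = 13, which already includes weeks 12 and 52
- week 26: 1

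Total: 1 + 1 + 6 + 13 + 1 = 22, which reproduces the stated figure. Stopping at week 52 gives 21. The scheduled visits therefore end at week 52 to 56, and none fills a second year.

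**2. Criterion 8 read literally.** The study ends at week 52. Twelve further months give 52 + 52 = week 104, twice the study period.

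**3. Effect on the recruitment rate.** Let N families be eligible on the week-52 reading and E of them enroll. Suppose the literal reading removes k families, of whom j would have enrolled. The rate changes from E/N to (E − j)/(N − k). It rises if j/k is below E/N and falls if j/k is above it. The article gives no value for j or k, so the direction is unknown. The other route to feasibility, six patients in under 36 months, can only become harder with fewer eligible families.

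**4. Age at which the 18th birthday precedes week 52.** Latest age = 18 − weeks/52.18.

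| Interval | Weeks | Latest age (years) |
|---|---|---|
| Surgery to week 52 | 52 | 17.00 |
| Surgery to end of the week-52 window | 54 | 16.97 |
| Enrollment to final visit, shortest (4 + 50) | 54 | 16.97 |
| Enrollment to final visit, nominal (8 + 52) | 60 | 16.85 |
| Enrollment to final visit, longest (12 + 54) | 66 | 16.74 |
| Surgery to literal end of criterion 8 | 104 | 16.01 |

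The enrollment rows assume that Table 3's week 8 ± 4 means weeks before surgery.

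**5. How often this could arise.** The article gives no age distribution, so ages at surgery are assumed uniform and independent.

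- Eligibility ends at the 18th birthday: 1 of 11 years of age is affected. Expected number 6 × 1/11 = 0.55. Chance of at least one: 1 − (10/11)^6 = 0.436.
- Eligibility includes 18-year-olds: 2 of 12 years are affected, counting those already 18. Expected number 6 × 2/12 = 1.0. Chance of at least one: 1 − (10/12)^6 = 0.665.

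**6. What a missing week-52 assessment would mean, if one occurred.** Each patient is 1/6 = 16.7% of the sample. One missing leaves 5/6 = 83%; two leave 4/6 = 67%. The article's threshold for completion of clinical outcome data is 80%. If that is counted per patient, which is an assumption, one missing patient still meets it and two do not.

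**The case against.** **On criterion 8.** The trial period is clear from four other places and no endpoint or analysis depends on this criterion, so it may be only a slip of wording. The phrase may also have been meant to secure attendance at device follow-up after the trial, which Table 3 does foresee. Both points stand. They limit the severity and mean the fix must allow for the second intention. They do not remove the contradiction, because this is operative eligibility text and its literal meaning conflicts with exclusion criterion 4.

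A reader might infer that criterion 8 inflates the recruitment rate by restricting the denominator to the most compliant families. The article does not support this. Ineligible families leave the numerator as well as the denominator, and nothing shows how often they would have enrolled.

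**On age.** The sentence containing "Ongoing follow-up for safety and DBS programming will occur at HSC until participants turn 18 years old" closes a paragraph that has already set out the trial visits, so it can be read as describing care after the trial. No passage says that study assessments stop at 18. Under Data management and statistical analysis, questionnaires may be completed online or on paper, and Table 3 marks the weekly and four-weekly neurosurgery evaluations as virtual. A full protocol may also cover the transition. These arguments carry weight and make the age point the weaker of the two.

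What remains is that the sentence follows directly on the in-trial programming visits at weeks 12, 26 and 52, names safety and programming, and makes no exception for participants still within their 52 weeks. A reader might go further and conclude that the plan builds in loss of week-52 data. That would require every 18th birthday to mean a missed assessment, which the article nowhere states.

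**Conclusion.** The contradiction in criterion 8 is established by the text alone: literally about week 104, against a study ending at week 52. Applied as written, it could exclude families able to complete the trial, and it makes the eligible denominator ambiguous. The size and direction of any effect on the recruitment rate cannot be determined from the article.

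The age point holds with lower confidence. Anyone aged about 17 or over at surgery turns 18 before week 52, and the article does not say how that participant is followed. The 44% to 67% range rests wholly on the assumed uniform ages and on the two readings of the upper age limit. It is the chance that at least one of six participants is 18 before week 52, and should not be quoted as a probability of data loss.

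Taken together the severity is minor to moderate: two passages to reconcile, with no error in the endpoint or the analysis.

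**What to change.** 1. Reword criterion 8 so that the ability to comply runs for 12 months following surgery, to week 52, in line with exclusion criterion 4. If attendance at post-trial device follow-up was also intended, state it separately from compliance with the trial.
2. Reconcile inclusion criterion 1 with the Follow-up section by stating that study assessments and adverse-event collection continue to week 52 for every participant regardless of the 18th birthday. Where clinical care is delivered is for the clinical team to decide.
3. If screening has begun, record which reading of criterion 8 was used, so that the eligible count can be interpreted.

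The cost is about two sentences in an amendment and a line in the screening record. The one practical burden is possible study follow-up of a participant after transfer to adult care.
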